#### Statistical analysis for portal-based measures

*Depression screening*. The scores from the patient health questionnaire—9, which range from 0 to 27, will be analyzed using generalized estimating equations (GEE) to account for repeated measures and cluster effects. The proportion of participants identified with mild, moderate, and severe depression will be compared over time and by intervention group. Logistic regression will assess the odds of timely referral for those flagged through the screening. The proportion of participants with depression identified and referred for further evaluation, and percentage of depression cases identified through the portal compared to standard care.

*Contraceptive use screening*. Responses to the contraceptive needs assessment will be analyzed descriptively with logistic regression models exploring factors associated with successful referrals for contraceptive services. The proportion of participants screened and successfully referred for contraceptive use will be tracked and compared between portal-based and standard care. Proportion of contraceptive requests from the portal and successful referrals, compared to total requests made through both portal and standard care.

*Tuberculosis screening*. Screening results for TB will be analyzed using logistic regression to compare referral rates between those screened via the portal and those using standard care. Time to referral following a positive TB screen will be analyzed using Cox proportional hazards models. The proportion of TB cases identified and referred through the portal and percentage of total TB cases identified overall during the study period.

*Alcohol and substance use screening*. Screening data from the CRAFFT (car, relax, alcohol, forget, friends, trouble) tool will be analyzed using GLMMs to assess differences in substance use disorder identification rates between portal and non-portal groups. The proportion of positive screens and subsequent referrals to intervention services will also be compared across the study periods. Percentage of alcohol and substance use cases identified through the portal and successful referrals for follow-up services will be compared to usual care.

*Time to service fulfilment*. Additionally, the time to service provision and HCP responsiveness to screening-related service requests will be compared between portal users and standard care groups using survival analysis techniques. These analyses will help determine the effectiveness and efficiency of integrating digital screening tools within the myCareHub platform in comparison to traditional care pathways.

*Qualitative data on end user experience*. Thematic analysis will be conducted on qualitative insights derived from FGDs to explore participant experiences, usability, and acceptability of the portal. The analysis will follow the six-phase approach to thematic analysis, which involves familiarization with the data, generating initial codes, searching for themes, reviewing themes, defining and naming themes, and producing the final report [18].

*Cost analysis*. Operational costs and other expenses related to the portal, such as server maintenance, technical support, and staff training, will be tracked for cost analysis. This detailed tracking will enable a comprehensive assessment of the financial feasibility and sustainability of scaling up the platform.

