### Outcome measures

Outcome parameters will be measured at the individual level at pre-specified time points: baseline, every 3 months, and end-line (Table 5). These measurements will be captured using digitized case report forms (CRFs) to ensure accuracy and consistency in data collection.

**Table 5 pdig.0000380.t005:** Summary of outcome variables and analysis measures.

Variable	Definition	Units	Source	Measurement Level	Measurement Period	Comparison Groups	Analysis
PAM	Patient activation measure	100-point scale	PAM-13	Individual	Baseline, 3, 6 and 9 months	Intervention versus Control	Mean change in PAM
Self-reported medication adherence	Estimate of adherence on 0–100% scale	Proportion	Visual analogue scale and adherence questionnaire	Individual	Baseline, 3, 6 and 9 months	Intervention versus Control	% adherence
Viral load suppression (VLS)	Proportion with viral load below detection limit	Proportion	Electronic medical record	Individual	Baseline, 3, 6 and 9 months	Intervention versus Control	% VLS
Cluster retention	Active in care at the end of reporting period/active at the beginning of the period*100	Proportion	Program data	Cluster	Baseline, 3, 6 and 9 months	Intervention versus Control	% retention
Cluster VLS	Percent viral load suppression within cluster	Proportion	Program data	Cluster	Baseline, 3, 6 and 9 months	Intervention versus Control	% VLS
Mobile health application usability score	Numerical score	Mean score	mHealth App Usability Questionnaire (MAUQ)	Individual	End-point	Intervention	Mean scores
Mobile health service acceptability score	Likert-like scale and text	Sub-section scores	Custom acceptability tool	Individual	End-point	Intervention	Mean scores
Social support	Six questions on social supporters	Number of supporters and ratings of support	Social support questionnaire-6 item (SSQ-6)	Individual	Baseline	Intervention	Baseline SSQ-6 scores
Tuberculosis (TB) intensified case finding tool (ICF)	4 questions each scoring 0 or 1	0–4	Portal TB ICF tool, Paper-based TB ICF tool, Program reports	Individual	Continuous	Intervention versus Usual care	% cases diagnosed
							Median time to TB diagnosis
Screening for depression	9 questions each scored 0–3 for total possible score of 27	0–27	Portal patient health questionnaire (PHQ-9)	Individual	Continuous	Intervention versus Usual care	% cases diagnosed

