## Results

This study will assess the impact of myCareHub on patient activation, medication adherence, social engagement and viral load suppression among AYP living with HIV. We anticipate improvements in these areas:

Patient activation—we expect that regular interaction with health diaries, reminders, and screening tools through the myCareHub platform will lead to increased PAM scores in the intervention group, indicating higher levels of patient engagement and activation in managing their health.Social engagement—increased use of online communities through the platform is expected to boost SSQ6 social engagement scores, particularly among those who may face barriers to in-person social interactions.Adherence and viral load suppression—with regular notifications and health management tools, we expect higher medication adherence rates and improved viral suppression among participants who use the portal consistently compared to those in the control group.

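### Several screening, referral and service-time comparisons group participants by portal use after crossover, not by the cluster's allocated period as Table 5 implies

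*Protocol article*

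**What the plan says.** Under Study design and its justification, clusters are randomised to one of three sequences that fix when they move from control to intervention. In Outcome measures, Table 5 gives the comparison for the five screening tools as "Intervention versus Usual care".

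Statistical analysis for portal-based measures then describes the comparisons as follows:

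- **Tuberculosis:** logistic regression to "compare referral rates between those screened via the portal and those using standard care".
- **Alcohol and substance use (CRAFFT):** mixed models for "differences in substance use disorder identification rates between portal and non-portal groups". Positive screens and referrals are also compared across study periods.
- **Contraception:** screening and successful referral are "compared between portal-based and standard care".
- **Depression:** severity categories "will be compared over time and by intervention group", but case identification is reported as the "percentage of depression cases identified through the portal compared to standard care".
- **Time to service fulfilment:** service times and provider responsiveness "will be compared between portal users and standard care groups using survival analysis techniques". The same paragraph says that these analyses will help establish how effective and efficient the digital screening tools are relative to traditional pathways.

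The Discussion names comfort with technology as a driver of portal engagement, and device access and connectivity as drivers of drop-out.

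**The concern.** Randomisation protects one contrast: cluster-periods after crossover against cluster-periods before it. Being screened through the portal, or being a portal user, is settled after crossover by the participant and the clinic. People who engage with a self-management app may differ in how readily they take up a referral, how often they screen positive and how quickly they attend. A contrast built on use mixes those differences with any effect of the portal.

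The two groupings do not coincide. Under Additional screening tools, the protocol says that the same instruments are already part of standard care. A participant in an intervention period can therefore be screened in the clinic and, on the tuberculosis wording, belong with standard care.

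At stake is whether the screening and service-time results can be read as effects of introducing the portal, which is how the plan intends to read them.

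**Working it through.** The plan gives no figure on this point, so there is none to reproduce. The check has two parts.

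**1. How each comparison is grouped**

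| Measure | Table 5 | Analysis text |
|---|---|---|
| TB referral | Intervention / usual care | Route of screening |
| CRAFFT identification | Intervention / usual care | Portal / non-portal |
| CRAFFT positive screens and referrals | Intervention / usual care | Study periods (not use-based) |
| Contraceptive referral | Intervention / usual care | Portal-based / standard care |
| Depression severity | Intervention / usual care | Intervention group (not use-based) |
| Depression case identification | Intervention / usual care | Portal / standard care |
| Time to service | Not listed as such; the underlying tools are intervention / usual care | Portal users / standard care |

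Five comparisons depart from Table 5: TB referral, CRAFFT identification, contraceptive referral, depression case identification and time to service. For none of them does the text say where a participant in an intervention period who never used, or stopped using, the portal is counted.

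**2. Illustration of the bias when the portal has no effect**

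All inputs are assumptions, because the documents give no uptake or referral rates:

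- uptake u = 0.5, 0.7 or 0.9;
- referral probability 0.70 or 0.80 in people who would use the portal (p_U) and 0.60 in those who would not (p_N);
- half of person-time in intervention periods;
- no time trend.

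*By allocated period.* Both sides have the same mix, u·p_U + (1 − u)·p_N, so the difference is 0.

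*Users against control periods, non-users left out.* The difference is p_U − [u·p_U + (1 − u)·p_N] = (1 − u)(p_U − p_N).

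*Users against everyone else.* The comparison side holds all control time (weight 0.5) and non-users' intervention time (weight 0.5(1 − u)). Non-user types make up (1 − u)/(1 − 0.5u) of it, so the difference is (p_U − p_N)(1 − u)/(1 − 0.5u).

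| u | p_U, p_N | Non-users left out | Users against everyone else |
|---|---|---|---|
| 0.5 | 0.80, 0.60 | 0.5 × 0.20 = 10.0 points | 0.20 × 0.5/0.75 = 13.3 points |
| 0.5 | 0.70, 0.60 | 5.0 | 6.7 |
| 0.7 | 0.80, 0.60 | 6.0 | 9.2 |
| 0.7 | 0.70, 0.60 | 3.0 | 4.6 |
| 0.9 | 0.80, 0.60 | 2.0 | 3.6 |
| 0.9 | 0.70, 0.60 | 0.1 × 0.10 = 1.0 | 0.10 × 0.1/0.55 = 1.8 |

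The false difference is 1.0 to 10.0 points if non-users are left out and 1.8 to 13.3 points if they join the comparison side. It takes the sign of the user/non-user gap, so it would reverse if users were the less likely group.

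**The case against.** The strongest reply is that these are pathway measures by design. The portal logs its own request-and-fulfilment cycle, and how fast a portal request is met is a fair process question. Table 5 could also be taken as governing, with the analysis text as loose shorthand; handling of non-users may be left to a fuller plan. Much of this stands: portal-share and turnaround figures are legitimate descriptions. It does not rescue the comparative analyses. The text specifies logistic regression, mixed models and survival analysis between use-defined groups and draws effectiveness from them, and the tuberculosis wording, which turns on the route of screening, is hard to read as shorthand for allocation.

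A practical objection also has force. Referral and service-time outcomes exist only after a positive screen or a request, and Table 5 names only a portal tool as the source for depression, contraception, violence and CRAFFT screening. The fix has to respect both points.

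Two stronger readings are tempting but unsupported:

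- **That viral suppression will be analysed in users only.** Results does expect "improved viral suppression among participants who use the portal consistently compared to those in the control group", but that is a statement of expectation. Statistical analysis of secondary objectives and Table 5 both compare intervention with control, and the regression of outcomes on portal use is presented as exploratory. The Discussion's remark about confirming the portal's clinical role concerns adherence and viral suppression, not the screening contrasts.
- **That non-users will be moved to the control side or dropped.** The group labels suggest one or the other, but the document states neither.

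**Conclusion.** The concern holds for the five comparisons identified above. As worded, they rest on route or use after crossover, disagree with Table 5, and are open to a self-selection that the protocol itself acknowledges. They cannot support the effectiveness statement under Time to service fulfilment.

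The size cannot be derived from the documents. The 1 to 13 points shown are illustrative and depend on the assumed uptake, the assumed gap and, for users against everyone else, the assumed half share of intervention time. Near-complete uptake or a small gap would make the bias minor.

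The primary PAM outcome, the planned adherence and viral suppression comparisons, depression severity and the CRAFFT comparison across periods are not at fault. The point deserves correction but does not threaten the trial's main conclusion.

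**What to change.** In Statistical analysis for portal-based measures, including Time to service fulfilment:

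- Define the groups in every comparative analysis by the cluster's allocated period, before or after its crossover, in line with Table 5, and include period effects.
- Include all enrolled participants eligible for the outcome, whether or not they used the portal. For referral and service-time outcomes, that means everyone with a positive screen or a request, by either route.
- Keep the share of services delivered through the portal and portal turnaround times as descriptive or exploratory, and label any user-based contrast that way.

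In Results, reword the viral suppression expectation so that it matches the planned intervention-versus-control analysis.

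No extra participants are needed. There are two costs. Effects diluted by non-use will look smaller than a users-only contrast. Clinic-side screening records must also be used for both periods where available: tuberculosis already lists paper and program sources, but the other tools list only the portal, so some extra data capture may be needed. Any comparison with usual care already requires clinic-side data of this kind.

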Contraceptive use intention screening	4 questions	Yes/No	Portal screening tool	Individual	Continuous	Intervention versus Usual care	% users accessing contraceptives
Sexual and Gender Based Violence (SGBV) screening	4 screening questions	Yes/No	Portal SGBV screening tool	Individual	Continuous	Intervention versus Usual care	% survivors successfully identified
Alcohol and substance use disorder screening	6 screening questions	Yes/No, with score>2 indicating problem	Portal incorporated CRAFFT tool (Car, relax, alone, forget, friends, trouble)	Individual	Continuous	Intervention versus Usual care	% with alcohol use disorder identified
Online community engagement	User online activity and interactions	Usage logs, time spent on portal, feature usage	Analytical dashboard	Individual	Continuous	Intervention	Online engagement

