*Additional screening tools*. myCareHub users will have access to various screening tools on their health diary, including the tuberculosis (TB) case finding tool, patient health questionnaire– 9 (depression screening), gender-based violence screening, contraceptive need screening, and screening for alcohol and substance use disorders. These tools are free to use and are already integrated as part of the standard of care within the ART program. Once these tools are completed, HCPs will receive an in-app notification indicating a pending task, with an automated status response sent back to the user. Upon task completion at the clinic, the HCP will mark the task as fulfilled, triggering a second notification to the user. myCareHub will automatically track this process cycle, and at the end of the study, the proportion of services fulfilled through the portal will be summarized and compared with the total services offered to the same age group. The median time to diagnosis of TB through the portal will be calculated and compared to usual care.

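### The tuberculosis models in the analysis section use referral as the event, while the stated tuberculosis outcomes are diagnosis and time to diagnosis

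*Protocol article*

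**What the plan says.** The protocol article describes the TB screening outcome in three places.

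- **Outcome measures, Table 5 (TB row).** Measured on individuals, intervention versus usual care. The analysis column lists the percentage of "cases diagnosed" and "Median time to TB diagnosis".
- **Portal-based measures, Additional screening tools.** The time outcome is repeated: "The median time to diagnosis of TB through the portal will be calculated and compared to usual care".
- **Statistical analysis for portal-based measures, Tuberculosis screening.** Two models are named: "Screening results for TB will be analyzed using logistic regression to compare referral rates between those screened via the portal and those using standard care" and "Time to referral following a positive TB screen will be analyzed using Cox proportional hazards models". The paragraph closes with a summary that has no model and no stated comparison: "The proportion of TB cases identified and referred through the portal and percentage of total TB cases identified overall during the study period".

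For contraception, Table 5 gives the percentage of "users accessing contraceptives". The analysis section instead compares the proportion screened and successfully referred, and does not say what makes a referral successful.

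**The concern.** Referral and diagnosis are different events. Referral is a step in the care process; diagnosis is the result that Table 5 promises to compare. A model fitted to referral answers whether people were sent on more often or sooner. It does not answer whether more TB was found, or found earlier.

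The comparison differs too. Table 5 compares intervention with usual care, the contrast that the stepped wedge randomises. The logistic model compares people by screening route. The article says that the screening tools are already part of standard care, so someone in an intervention period could still be screened outside the portal, and the route actually used is not randomised. The Cox model narrows the population further, because its clock starts at a positive screen.

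What is at stake is interpretation. A favourable hazard ratio for referral could be read as the Table 5 result on time to diagnosis, which no named model estimates.

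**Working it through.** The documents state no rate, event count or power for the screening outcomes, so there is no figure to reproduce. The main check sets the statements side by side.

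| Feature | Table 5 and Additional screening tools | Analysis section, TB models |
|---|---|---|
| Event, proportion | TB diagnosed | Referred |
| Event, time | TB diagnosed | Referred |
| Contrast | Intervention or portal versus usual care | Screened via portal versus standard care (logistic); not stated (Cox) |
| Who is counted | Not restricted to positive screens | Those screened (logistic); positive screens (Cox) |

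Both events differ, and so does the population for the time outcome. Cases identified do appear in the analysis paragraph, but only as a proportion and a percentage. Time to diagnosis does not appear there.

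The later paragraph on time to service fulfilment plans survival analysis of service provision and provider responsiveness to screening requests. A fulfilled request is not a TB diagnosis, so this does not fill the gap.

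**How far referral can stand in for diagnosis.** Every input below is an assumption, and diagnosis is taken to follow only from referral.

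*Proportion, per person screened.* P(diagnosed) = P(positive screen) × P(referred given positive) × P(diagnosed given referred).

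- Assume 10% positive on the portal, 5% in usual care, and 90% of positives referred in both.
- Referred: 0.10 × 0.90 = 0.090 versus 0.05 × 0.90 = 0.045. Referral ratio 0.090 / 0.045 = 2.00.
- With a usual-care yield of 15% per referral, usual care diagnoses 0.045 × 0.15 = 0.00675.
- Portal yield 15%: 0.090 × 0.15 = 0.01350; diagnosis ratio 2.00.
- Portal yield 10%: 0.090 × 0.10 = 0.00900; diagnosis ratio 1.33.
- Portal yield 7.5%: 0.090 × 0.075 = 0.00675; diagnosis ratio 1.00.

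The logistic model would see the same referral contrast in all three cases.

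*Time.* Time to diagnosis = time to referral + lag from referral to diagnosis, both taken as exponential and simulated.

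- Median time to referral 1 day on the portal versus 5 days in usual care: hazard ratio for referral 5 / 1 = 5.0.
- With a median lag of 10 days in both, median time to diagnosis is 11.5 versus 17.7 days, a ratio of 17.7 / 11.5 = 1.54.
- With a portal lag of 14 days it is 15.5 versus 17.7 days.

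Even with equal lags, a fivefold referral hazard goes with a much smaller relative change in median time to diagnosis.

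**Contraception.** Access and successful referral differ as worded. If successful means that the service was received, they coincide; the article does not say.

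**The case against.** The strongest reply is that these are additional portal measures, that referral is a reasonable early marker, and that services received are partly covered elsewhere, through the fulfilment summary and the survival analysis of service provision. Much of this stands. It lowers the weight of the point and softens it for contraception. It does not supply a TB model with diagnosis as the event.

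A reader might also infer stronger claims, which the documents do not support.

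- **That depression has the same fault.** The analysis section compares depression severity categories by intervention group, and cases identified through the portal against standard care. Referral is an added measure there.
- **That the referral models would give the opposite answer.** This needs an assumed portal yield that is much lower (5% above gives a diagnosis ratio of 0.67) or an assumed lag that is much longer (20 days gives 21.5 versus 17.7 days). With equal yield and lag, both measures point the same way.
- **That the software itself creates referrals.** The article describes automatic service requests and provider notifications, but nowhere counts them as referrals.
- **That a median time to diagnosis can never be reached.** That holds only if every positive screen stays in the risk set and fewer than half prove to be TB. Among diagnosed cases a median exists.
- **That the fulfilment share is capped and therefore wrong.** The plan says "the proportion of services fulfilled through the portal will be summarized and compared with the total services offered to the same age group". If only enrolled participants use the portal, service rates are equal, and the denominator is all young people in Table 4 over four periods, the share is (186×4 + 170×3 + 124×2) / (2,356×4) = 1,502 / 9,424 = 15.9%. The article fixes none of these conditions, and a low share is no error in a descriptive summary.

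**Conclusion.** The point holds for TB. The stated outcomes are diagnosis and time to diagnosis, intervention versus usual care; both named models use referral, and the logistic model compares screening routes. This follows from the wording alone and needs no assumed rate. It holds conditionally for contraception, where one definition would settle it.

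The size cannot be derived from the documents. The illustration shows only that a given referral effect is compatible with a range of diagnosis effects, including none.

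Severity is minor. The abstract and Table 1 do not list the TB and contraceptive screens among the secondary outcomes, and neither the primary outcome nor the planned 480 participants depends on them.

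**What to change.** - **TB.** In the Tuberculosis screening paragraph, make TB diagnosis the analysed event, both as a proportion and as a time. Compare intervention with control periods among enrolled participants, use the same event definition in both conditions, and account for cluster and period.
- **Referral.** Keep referral and time to referral as process measures, labelled as such.
- **Contraception.** Either analyse the Table 5 measure of access, or state that a successful referral means the service was received.

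The change is rewording and needs no additional participants. The downside is precision: there will be fewer diagnoses than referrals, so the comparison may be able to give only an estimate with a wide interval.

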### Statistical methods

Statistical analysis of the primary and secondary endpoints will be conducted in either R or SAS using generalized linear mixed models (GLMMs), which allow for incorporation of correlations due to repeated measures, cluster effects, and potential time effects.

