#### Statistical analysis of secondary objectives

*Self-reported medication adherence*. Self-reported adherence scores, collected at baseline, 3, 6, and 9 months, will be analyzed using GLMMs. These models will account for correlations between repeated measures across the different time points and clustering effects within facilities. The percentage of adherence in the intervention versus control groups will be compared, with adjustments made for potential confounders such as age, sex, and ART duration.

*Viral load suppression*. The proportion of patients achieving viral load suppression (VLS) at baseline, 3, 6, and 9 months will be modeled using logistic regression, adjusted for cluster effects. A comparison between the intervention and control groups will be made, considering time effects and covariates. The percentage of participants in each group who achieve viral suppression will be reported, and changes over time will be assessed.

*Social engagement*. Social engagement scores (SES) from the SSQ6 will be compared across time points (baseline, 3, 6, 9 months) using mixed-effects models. Participation in online communities will be tracked and compared to baseline scores to assess whether the intervention effectively improves social engagement. Differences in social engagement over time will be explored, with subgroup analyses based on age, sex, and baseline social support.

*Portal use and engagement metrics*. The frequency of portal logins, time spent on the portal, and functionalities accessed will be analyzed using descriptive statistics. Regression models will be used to explore relationships between portal use and adherence, activation, and viral suppression outcomes. Portal use will be summarized as engagement metrics (e.g., total logins, average time spent) and correlated with clinical outcomes, including adherence and viral suppression.

*Usability and acceptability scores*. Usability scores from the MAUQ and the custom-designed acceptability survey will be analyzed using descriptive statistics and compared across subgroups (age, sex, ART duration). Generalized linear models will be used to explore the association between usability scores and primary or secondary outcomes. Usability and acceptability will be assessed and reported, with particular attention to how these factors influence engagement with the platform.

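### The TB referral and time-to-referral models are stated without cluster or calendar period, and the portal contrast is not the randomised one; omitting period would confound the portal with any drift in referral practice

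*Protocol article*

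**What the plan says.** All references are to the Protocol article.

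- *Statistical analysis for portal-based measures*, tuberculosis paragraph: the plan is "logistic regression to compare referral rates between those screened via the portal and those using standard care". For the time outcome, "Time to referral following a positive TB screen will be analyzed using Cox proportional hazards models".
- Same section, time-to-service paragraph: time to provision and provider responsiveness "will be compared between portal users and standard care groups using survival analysis techniques".
- Same section, depression paragraph: PHQ-9 scores "will be analyzed using generalized estimating equations (GEE) to account for repeated measures and cluster effects". The alcohol and substance use paragraph uses generalized linear mixed models.
- *Statistical analysis of secondary objectives*: viral suppression "will be modeled using logistic regression, adjusted for cluster effects", and the next sentence adds time effects and covariates.
- *Statistical methods*: primary and secondary endpoints get generalized linear mixed models, "which allow for incorporation of correlations due to repeated measures, cluster effects, and potential time effects". The portal-based measures have their own heading further on.
- Table 2 shows the rollout: every cluster in control at baseline, three crossover steps, and every cluster in intervention in the last two periods.

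**The concern.** The article names cluster effects, and for viral suppression also time effects, where it describes neighbouring outcomes. It names neither for TB referral or time to referral. An analyst who followed those two sentences literally would fit independent-observation models.

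Two things would then go wrong. First, how quickly a positive screen is acted on depends on clinic staff, so requests from one cluster are correlated and standard errors would be too small. Second, and more important here, exposure to the portal is tied to calendar time by the design. Any change in referral practice over the study, for reasons unrelated to the portal, would be counted as a portal effect.

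A third problem lies in the contrast itself. Patients screened through the portal are compared with those screened in standard care, and portal users with standard care. Those groups are formed by what patients actually did, so the comparison does not carry the protection of randomisation, and cluster and period terms would not restore it.

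**Working it through.** **Plan figures.** The article gives no event count, intracluster correlation (ICC), error rate or trend for these analyses, so there is no figure of its own to reproduce for them. The PAM sample size is the nearest anchor: 27 / (1 − 0.10) = 30 per cluster, and 16 × 30 = 480, as stated. Its ICC of 0.02 is for PAM and is borrowed below.

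**How far exposure is tied to time.** Number the periods 0 to 4. With the 6/6/4 split of Table 4, the clusters exposed are 0, 6, 12, 16 and 16 of 16.

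- Exposed cluster-periods: 6 + 12 + 16 + 16 = 50; mean period (6×1 + 12×2 + 16×3 + 16×4)/50 = 142/50 = 2.84.
- Control cluster-periods: 16 + 10 + 4 = 30; mean period (10×1 + 4×2)/30 = 18/30 = 0.60.
- Gap: 2.84 − 0.60 = 2.24 quarters.

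The 5/5/6 split of Table 2 gives 137/47 − 23/33 = 2.22 quarters.

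**Spurious effect if period is omitted.** With a ratio of *r* per quarter and no true effect, the apparent ratio is roughly r^2.24. For r = 1.10 this is about 1.24; for r = 1.25, about 1.65.

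**Approximate rejection rate.** Take 3 positives per cluster-period, so 3 × 16 × 5 = 240 in all, and ignore clustering. The exposed share is 50/80 = 0.625, and 0.625 × 0.375 = 0.234. The expected z at r = 1.10 uses log(1.24) ≈ 0.2135.

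- Cox, every positive referred in time: 0.2135 × √(240 × 0.234) ≈ 1.60, so the two-sided 5% test rejects in about 36% of trials.
- Logistic, assumed referral probability 0.6 (variance 0.24): 0.2135 × √(240 × 0.234 × 0.24) ≈ 0.78, so about 12%.

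**Simulation.** No intervention effect, 16 clusters (6/6/4), five quarterly periods, cluster and cluster-period random effects, cluster autocorrelation 0.5 or 0.9, rejection at |z| > 1.96, 1,500-2,000 runs per scenario. Type I error of the unadjusted tests at ICC 0.02:

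| Positives per cluster-period | Trend per quarter | Logistic | Cox |
|---|---|---|---|
| 0.3 to 3 | none | 3-6% | 6-7% |
| 10 | none | 6-7% | 8% |
| 30 | none | 8-9% | 12-14% |
| 1 | 1.10 | 7-8% | 13-14% |
| 3 | 1.10 | 12-13% | 32-34% |
| 10 | 1.10 | 28-29% | 75-76% |
| 3 | 1.25 | 40-41% | 90-91% |

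The 30-positive row would need every participant to count in every quarter. At ICC 0.10 with no trend, the rates are about 3-7% and 6-9% with up to 3 positives, and 19-25% and 30-35% with 30. The 5/5/6 split gives nearly the same: 12.1% and 33.6% at 3 positives and trend 1.10.

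**With cluster and period in the model** (logistic with fixed effects for both; Cox stratified by cluster with period terms), at 3 positives, ICC 0.02 and trend 1.25: 5.0% and 5.8% in 400 runs, against 39.8% and 91.1% unadjusted. The Monte Carlo standard error is about √(0.05 × 0.95/400) = 1.1 percentage points.

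**The case against.** The best case for the authors has four parts.

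*Silence is not exclusion.* A reader might infer that clustering and period will be ignored. The article does not say so. It is a condensed account, an analysis plan may exist, and survival techniques include frailty, stratified and robust-variance models. The abstract also says in general terms that mixed models will be used with adjustment for clusters. This stands in part. The time-to-service sentence is unspecific rather than wrong. But the abstract's sentence covers neither Cox models nor period, the rule in *Statistical methods* is confined to primary and secondary endpoints, and the TB sentences fix named models where their neighbours state the adjustment.

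*The inflation may be small.* A reader might also infer that the false-positive rate is well above 5% as a matter of fact. The article's figures do not show that. At its only ICC, with few positives and no trend, the rate stays near nominal. Large inflation needs an assumed trend, or a higher ICC with many requests. This stands fully.

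*The comparator may be concurrent.* Table 5 contrasts intervention with usual care and lists paper tools and program reports as TB sources. The cluster totals in Table 4 sum to 2,356 young people against 480 participants. If non-participants in the same clinics and quarters supply the usual-care data, part of the comparison is within cluster and period and the simulated inflation would not carry over. This also stands, but it makes the contrast more clearly non-randomised.

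*The measures are supporting ones.* No alpha or confirmatory role is set for them, and the PAM, adherence and viral suppression analyses are untouched. That limits the consequence.

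**Conclusion.** The point holds as a matter of specification. The two TB models are stated without cluster or period, unlike viral suppression (both named) and PHQ-9 (clusters named), and time to service is left open. Because exposed cluster-periods fall on average about 2.2 quarters later than control ones, leaving period out would confound the portal with any secular change in referral.

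The size is conditional. It is about 12-13% (logistic) and 32-34% (Cox) under an assumed trend of 1.10 per quarter, ICC 0.02 (borrowed from PAM), 3 positives per cluster-period and exposure defined by the rollout. It is about 3-7% from clustering alone with few positives and no trend. The trend, the referral probability and the number of positives are all assumptions.

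Separately, and without any such assumption, the contrast by actual portal use is not the randomised comparison. The consequence is confined to supporting measures, but the article intends them to inform the judgement on how well the screening tools work.

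**What to change.** - **Referral:** a logistic mixed model with a random cluster effect and categorical calendar period.
- **Time to referral and time to service:** Cox models with shared cluster frailty or cluster-robust variance, stratified by or adjusted for period. With 16 clusters, robust variance needs a small-sample correction. Where a participant makes repeated requests, account for that too.
- **Exposure:** randomised condition (control or intervention period of the cluster) as the main exposure. State who forms the usual-care group, and label any comparison of portal users with usual care as observational.
- **Sparse events:** if there are too few for these models, report counts, proportions and median times without p-values.

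The cost is a few sentences of text and slightly wider intervals. No extra participants are needed. An analysis by randomised condition does need screening and referral dates from control periods; the article says these tools are already part of standard care, so the records to draw on should exist.
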